**Not related**

- The event is clearly related to other factors such as the subject's clinical state, therapeutic interventions, or concomitant drugs administered to the subject.

**Possibly Related**

- The event follows a reasonable temporal sequence from the time of drug administration,
- And/or follows a known response pattern to the trial drug,
- **But** could have been produced by other factors such as the subject's clinical state, therapeutic interventions, or concomitant drugs administered to the subject.

**Related**

- The event follows a reasonable temporal sequence from the time of drug administration,
- **And** follows a known response pattern to the study drug,
- **And** cannot be reasonably explained by other factors such as the subject's clinical state, therapeutic interventions, or concomitant drugs administered to the subject,
- **And** either occur immediately following trial drug administration, **or** improves on stopping the drug, **or** reappears on repeat exposure, **or** there is a positive reaction at the application site.

It is up to the discretion of the Investigator, in the event of an AE or SAE, to temporarily discontinue study medication or to discontinue the subject from the study. The end of study examinations / samplings must be performed if the subject is discontinued from the study.

**9.2 Reporting Serious Adverse Events**

A serious adverse event (SAE) related to the study drug is defined as any adverse drug experience occurring at any dose that results in any of the following outcomes:

- Results in death,
- Is life-threatening (NOTE: The term "life-threatening" in the definition of "serious" refers to an event in which the subject was at risk of death at the time of the event; it does not refer to an event which hypothetically might have caused death if it was more severe).
- Results in inpatient hospitalization or prolongation of existing hospitalization,
- Results in a persistent or significant disability/incapacity, or
- Results in a congenital anomaly/birth defect.

Important medical events that may not result in death, be life-threatening, or require hospitalization may be considered a serious adverse drug experience when, based upon appropriate medical judgment, the event may jeopardize the subject and may require medical or surgical intervention to prevent one of the outcomes listed in this definition.

Any SAE occurring during the study (from receiving informed consent until end of study) or within 30 days after study completion will be reported to the Sponsor within 24 hours of knowledge of the event.

In the event of an SAE, the SAE/DSM form available in the electronic Trial Master File (TMF) is to be completed and reported to UBC Geneva by fax ([contact] or [contact]) within 24 hours of learning about the event regardless of whether all information is known. An e-mail will also be sent to [[contact]](mailto:[contact]) to inform about the SAE.

Initial SAE reporting can be done by telephone with written reports to follow by fax within 24 hours.

All SAEs must be followed until resolution (subject has returned to baseline status of health), or until stabilization (the investigator does not expect any further improvement or worsening of the reported event).

## 10 STUDY MANAGEMENT

A total of 210 subjects, according to the following schedule:

- First subject enrolled: [20160915]
- [35] subjects enrolled: [20170501]

- 918 • [70] subjects enrolled: [20170715]
- 919 • [140] subjects enrolled: [20171215]
- 920 • [210] subjects enrolled: [20180501]
- 921 • Last subject completed: [20180901]

922

### 923 **10.1 Subject Discontinuation**

924 A discontinuation occurs when an enrolled subject ceases participation in the study,  
925 regardless of the circumstances, prior to completion of the protocol.

926

927 The investigator has the right to remove a subject at any time if it is in the best medi-  
928 cal interest of the subject.

929

930 Subjects will be discontinued from treatment prior to completion for any of the fol-  
931 lowing reasons:

932

- 933 • Consent withdrawn / the parents/guardians wish to discontinue study treat-  
934 ment
- 935 • AE (clinical events or laboratory values) that contraindicate continuing the  
936 study.
- 937 • Best interest of the patient, as judged by the Investigator
- 938 • Protocol violation
- 939 • Administrative Decision
- 940 • Other, by Investigator specified reason

941

942 Subjects withdrawn from the study for a SAE should be followed until the SAE has  
943 resolved. Appropriate supportive and/or definitive therapy should be administered as  
944 required.

945

946 The investigator must determine the primary reason for discontinuation. The reason  
947 for a subject discontinuing from the study will be recorded on the case report form.  
948 Withdrawal due to an adverse event should be distinguished from withdrawal due to  
949 other reasons, according to the definition of an adverse event noted earlier. A discon-  
950 tinuation must be reported immediately to UBC Geneva by fax ([contact] or  
951 [contact]) if it is due to a serious adverse event.

952

953 The **End of Study** examination / sampling must be performed at the time of the study  
954 discontinuation. The investigator will record the reason for study discontinuation,  
955 provide or arrange for the appropriate follow-up (if required) for such subject, and  
956 document the course of the subject's condition.

957

### 958 **10.2 Study Termination**

959

960 Termination of the study before all subjects have been enrolled can occur for any of  
961 the following reasons:

962

- 963 • it was determined that the risk level associated with the experimental drug was  
964 significant and warranted termination of the study;

- the sponsor terminated the study for any reason, at any time, by written notice of intended termination;
- the principal investigator, EPN terminated participation of that clinical site in the study by written notice;
- any other clause in the individual site Clinical Study Agreement was not met

### 10.3 Data Recording

Source documents are original documents, data, and records from which the subject's case report form (CRF) data are obtained. These may include but are not limited to hospital records, clinical and office charts, laboratory and pharmacy records, diaries, microfiches, radiographs, and correspondence. All original source documents supporting entries on CRFs must be maintained and be readily available.

The investigator will record all data with respect to the study in the subject's CRFs. This includes but is not limited to study procedures, laboratory data, safety-related data and drug accountability.

The investigator will sign and date the indicated places on the CRFs. These signatures will signify that the investigator inspected or reviewed the data on the CRF and on the data queries and that he/she agrees with the content.

All corrections on a CRF and on source documents must be made in a way that does not obscure the original entry. The correct data must be inserted, dated and initialed by study center personnel. If the reason for the change is not obvious, an explanation should be provided.

### 10.4 Case Report Forms

The Investigator will complete Case Report Forms for all subjects. These are to be completed in English. If a test/assessment is not done and will not be available, indicate this by writing "N/D" (Not Done) in the respective answer field in the CRF. If the question is irrelevant (e.g. is not applicable) indicate this by writing "N/A" (Not Applicable) in the respective answer field.

Corrections of data can only be made by crossing out the incorrect data and writing the correct data next to those crossed out (e.g. 352 325). Erasure by any method is not allowed. Any changes in the CRF by the Investigator or his/her delegate must be signed with initials, dated and explained (if necessary). If corrections are made by the Investigator's authorized staff after the date of the Investigator's signature on the CRF, the CRF must be signed and dated again by the Investigator. Corrections necessary after the CRFs have been removed from the Investigator's site must be documented on a Data Clarification Form (DCF).

Original source documents, case report forms, and other study documentation will be maintained at the study site as specified.

Completed original Case Report Forms are the property of the Sponsor.

## 10.5 Training

The Investigator will ensure that appropriate Good clinical practice training relevant to the study is given to the medical, nursing and other staff involved. Any information of relevance to the performance of this study is to be forwarded to the co-investigator and other staff involved.

All investigators signing the protocol and key personnel should provide signed and dated Curriculum Vitae (CV) originals to be filed by the Sponsor. The CV should include name, title, occupation, education, research experience and present and former positions. A staff signature list including delegation responsibilities is required and will be continuously up-dated.

## 10.6 Source Data

Source data will be collected in the "Source Data File". The Source Data File should contain raw data from examinations/samplings/laboratory results required to verify the data entered into each patient's CRF.

The following data will be recorded directly on the electronic CRFs and will be considered source data: gender, age, length, weight, HC, medical history, physical examination and retinal scan.

The hospital records should clearly indicate at least:

- that the patient participated in the study (by patient identification and study identification)
- when the written informed consent was obtained,
- all examinations/samplings/laboratory results of importance for the patient's clinical care and
- serious adverse events.

## 10.7 Quality Assurance

The data will be entered into a database, where internal review and programmed computer checks will be used to identify selected protocol violations and data errors. If necessary, requests for clarifications or corrections will be sent to the investigator.

The investigator agrees to monitoring of the study by a Sponsor representative and that Regulatory Authorities will have the right from time to time both during and after the course of this trial to inspect the study and review pertinent medical records relating to this clinical trial.

Before, during and after the study, the monitor will have regular contacts with the clinic including visits to confirm that facilities remain acceptable, that the investiga-

tional team is adhering to the protocol, that data are being accurately recorded in the CRF and to provide information and support to the Investigator. Monitoring of the study will be carried out by clinical research manager [name], Institute of Neuroscience and Physiology, University of Gothenburg according to their Standard Operating Procedures (SOP).

A statement will be obtained from each subject's parents/guardians participating in the trial permitting the release of the subject's medical records as necessary for monitoring or inspection by authorized personnel for the Sponsor and Regulatory Authorities.

The investigator is responsible for maintaining a comprehensive and centralized filing system of all study-related (essential) documentation, suitable for inspection at any time by representatives of the Sponsor and Regulatory Authorities.

## **10.8 Protocol Amendments**

All revisions to the protocol should be reviewed and approved by the Sponsor prior to submission of the amendment to the regulatory authorities. If the revision is an Administrative Change, the investigator should submit it to the EPN for their information. If the revision is an Amendment to the protocol, the Investigator must sign it to verify he/she has read and understands the change. The investigator must submit the Amendment to the EPN for review and approval prior to implementation.

If an amendment substantially alters the study design or increases the potential risk to the subject:

- the informed consent form or subject information sheet must be revised and submitted to the EPN for review and approval; and
- the approved revised form must be signed by both parents/guardians currently enrolled in the study; or
- the new form must be used to obtain consent from new parents/guardians prior to their enrollment into the study.

## **10.9 Retention of Study Records**

ICH-GCP guidelines require the medical records and notes, etc., should be clearly marked and permit easy identification of participation by an individual in the trial.

The files should be archived by the investigator at least 10 years after the study is finished.

The investigator is to record all data with respect to protocol procedures, drug administration, laboratory data, safety data, and efficacy data on the CRFs. Essential documents should be retained until at least 2 years after the last approval of a marketing

application in an ICH region and until there are no pending or contemplated marketing applications in an ICH region or at least 2 years have elapsed since the formal discontinuation of clinical development of the investigational product. The investigator should store the study records in a secure location.

## **11 DATA MANAGEMENT AND STATISTICAL METHODS**

The investigator will record all data with respect to the study in the subject's CRFs. This includes, but is not limited to, study procedures, laboratory data and safety-related data.

All corrections on a CRF and on source documents must be made in a way that does not obscure the original entry. The correct data must be inserted, dated and initialed by study center personnel. If the change is not obvious, an explanation should be provided.

Completed CRFs for this study will be forwarded to the sponsor for editing, construction of a quality-assured database, and analysis of the data.

Descriptive and analytical statistics will be used.

### **11.1 Determination of Sample Size and Statistical Methods**

#### **Primary endpoint**

The mean incidence of any ROP in an age-matched population (22 weeks + 0 days to 27 weeks + 6 days of GA at birth) in Sweden during the years 2008 – 2012 is calculated to 42%. Assuming an alpha of 5%, a power of 80% and a 50% reduction in incidence of any ROP, i.e. from 42% to 22%, a sample size of 80 subjects per treatment group is required. The reduction in any ROP with AA:DHA supplementation is based on efficacy in previous publications (33).

A total of 105+105 subjects will be included to compensate for protocol violations (experience gained in pilot study) and drop-outs (e.g. a perinatal death rate of approximately 15% at these gestational ages).

After the first 10 subjects have been treated, we will perform pharmacokinetic analyses with respect to fatty acid concentrations in serum.

After the first 30 subjects have been treated and evaluated a safety data committee will perform an evaluation to confirm that the safety profile is acceptable and that the assumption of a reduction in ROP incidence is reasonable.

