## 2 RATIONALE

### Preterm Child

We have performed a randomized pilot study of 78 infants (in manuscript) comparing SMOFlipid with Clinoleic. We found no effect of SMOFlipid on ROP outcome. Infants on SMOFlipid had less loss of fraction of DHA than those on Clinoleic while fraction of eicosapentaenoic acid (EPA) increased substantially compared to cord blood and AA fell more in the SMOFlipid than in the Clinoleic group. No reduction of EPA fraction was found in the Clinoleic group. Concerns have previously been raised regarding the use of fish oil to preterm infants since both DHA and EPA may have a negative impact on proportion of AA which is thought to promote growth. No adverse effects of giving preterm infants fish-oil in SMOFlipid have been reported (1). However, raising EPA fraction and reducing AA fraction during a period of rapid growth and development appears inappropriate. We will therefore study whether a combination of AA and DHA in addition to Clinoleic compared with Clinoleic alone reduces ROP and other morbidities in extremely preterm infants and improves outcome. At present, no lipid solution for parenteral use containing significant amounts of AA and DHA is available. Instead DHA from algae and AA from fungi (Formulaid™) (DSM) are available for enteral administration. These lipids are included in preterm formula, have been given early to very preterm infants and were well tolerated (10).

The effect of different doses of DHA to preterm infants has been studied and approximately 50-80 mg/kg/day appears appropriate (43, 44). Less is known about AA needs, but in a Norwegian study 47 mg/kg/day added to breast milk resulted in less decrease in the proportion of AA in serum fatty acids (6%) than with breast milk only (24%). It was concluded that the AA dose was probably too low (43).

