### 1.4 Sample Size

The sample size text below is provided in the study protocol version 7b.

The mean incidence of any ROP in an age-matched population (22 weeks + 0 days to 27 weeks + 6 days of GA at birth) in Sweden during the years 2008 – 2012 is calculated to 42%. Assuming an alpha of 5%, a power of 80% and a 50% reduction in incidence of any ROP, i.e. from 42% to 22%, a sample size of 80 subjects per treatment group is required. The reduction in any ROP with AA:DHA supplementation is based on efficacy in previous publications.

A total of 105+105 subjects will be included to compensate for protocol violations (experience gained in pilot study) and drop-outs (e.g. a perinatal death rate of approximately 15% at these gestational ages).

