## 3.2 Efficacy Variables

### 3.2.1 Primary Efficacy Variable

Primary efficacy variable in this study is occurrence of sight threatening ROP (ROP stage 3 or worse). All randomized infants will be included in the evaluation of the primary variable. Early drop-outs and deaths before evaluated ROP stage 3 or worse will be considered as non-events and will contribute with their follow-up time in the analysis of comparisons between event rates using Poisson regression. A sensitivity analysis will analyse primary efficacy variable applying survival analyses adjusting for death as competing risk and censoring of those infants that have dropped out due to other reasons than death.

In this study ophthalmologic assessment of ROP stage was performed in blinded manner. Retinal examination were performed approximately once weekly starting at four to five weeks of age according to a standardized protocol and to clinical screening praxis. The evaluation of ROP occurred independently from the study and paediatric ophthalmologists were unaware of which infants were participating in the study.

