## 4 STATISTICAL METHODOLOGY

### 4.1 General Methodology

For continuous variables mean, Standard Deviation (SD), median, minimum and maximum will be presented, or median and Interquartile Range (IQR) as applicable, and for categorical variables number and percentage.

The baseline characteristics will be described; inferential statistics will be performed and interpreted descriptively only.

The confirmatory analyses will be only performed for:

1. Primary efficacy variable, impact of IP on severe ROP (comparison of event rates)
2. Secondary efficacy variable, impact of IP on overall levels of AA (mol%) continuously over time
3. Secondary efficacy variable, impact of IP on overall levels of DHA (mol%) continuously over time
4. Secondary efficacy variable, impact of IP on BPD (yes/no at PMA week 36, comparison of event rates)
5. Secondary efficacy variable, impact of IP on IVH (grade 0-4)

For those analyses the difference in the estimates and their 95% Confidence Intervals (CI) will be provided, and tests will be adjusted for multiplicity according to the fix sequential method as per the sequential order above. This methods allows for the significance mass of 0.05 to be inherited to the next variable in order and the testing is stopped when non-significance is achieved.

|                                     |  |                                    |               |
|-------------------------------------|--|------------------------------------|---------------|
| STATISTISKA KONSULTGRUPPEN          |  | Statistical Analysis Plan          |               |
| Protocol:
Mega Donna Mega |  | Protocol No:
MEGADONNAMEGA 16-7 |               |
|                                     |  | Version:
1.0                    | Page 17 of 21 |

Missing data will be handled according to the section 3.2.

All other analyses will be considered as exploratory, 95% CI will be provided for the difference between the groups and p-values will be given only for descriptive purpose.

All tests will be two-tailed and confirmed analyses will be conducted at 0.05 level applying fix sequential testing. All analyses will be performed using SAS software version 9.4 (SAS Institute Inc., Cary, NC, USA).

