## 6 CHANGES OF ANALYSIS FROM PROTOCOL

No changes to protocol version 7b have been done. However, no detailed description of the analyses were available in the protocol. All analyses specified within this SAP are aimed to be conservative regarding the IP and applying ICH and EMA guidelines for statistical analyses and adjustments. Additionally, recently published guidelines from ASA and NEJM have been employed.

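### The trial's only power statement is for any ROP, but the primary test is of ROP stage 3 or worse, for which no control rate, effect or power is given

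*Combined protocol and SAP*

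**What the plan says.** **Sizing.** Protocol 11.1, under its primary endpoint heading, starts from "The mean incidence of any ROP in an age-matched population" in Sweden in 2008–2012, put at 42%. It continues "Assuming an alpha of 5%, a power of 80% and a 50% reduction in incidence of any ROP, i.e. from 42% to 22" per cent and concludes that "a sample size of 80 subjects per treatment group is required". Enrolment is raised to 105 per arm for protocol violations and drop-outs, including a perinatal death rate of about 15%. SAP 1.4 repeats the calculation, introduced by "The sample size text below is provided in the study protocol version 7b".

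**Testing.** SAP 3.2.1 states: "Primary efficacy variable in this study is occurrence of sight threatening ROP (ROP stage 3 or worse"). SAP 4.1 puts severe ROP first in its five-step confirmatory sequence. SAP 4.6.1 analyses it by Poisson regression adjusted for centre and gestational-age category.

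**Elsewhere in the protocol.** The aims (synopsis and section 3) speak of ROP as a sight-threatening disease. Section 11.4 refers to evaluating stage 3 or more. The synopsis lists ROP incidence and severity among the efficacy endpoints.

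**Changes and remaining endpoints.** SAP section 6 states "No changes to protocol version 7b have been done", while noting that the protocol held no detailed description of the analyses. Any ROP is not an efficacy variable in SAP 3.2.1 or 3.2.2, and 3.2.3 says there are no others for the first publication. Stages 1 and 2 appear only in the adverse-event classification in 3.3.2.

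**The concern.** A power figure is a property of one endpoint, one assumed effect and one test. Here the 80% is attached to any ROP, while the hypothesis tested first is stage 3 or worse. Severe disease is rarer than all disease in the same infants, so for the same relative effect there are fewer events and less power. A reader of SAP 1.4 and 3.2.1 together could take the primary test to be 80% powered, and could give a non-significant result more weight than the design supports.

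The endpoint that fixed the sample size also drops out of the efficacy analysis, so the stated design assumption would not be tested in the first publication. The protocol is not consistent on which endpoint is primary, and the SAP does not say which part of it was followed.

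**Working it through.** **Inputs.** From protocol 11.1: 42% v 22%, alpha 5%, power 80%, 80 per arm, 105 enrolled per arm, about 15% deaths. Allocation is 1:1. The protocol's sizing text does not state sidedness; SAP 4.1 says "All tests will be two-tailed". The control rate for stage 3 or worse is **not in the documents** and is varied below as an assumption.

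**Step 1: reproduce the stated figure.** With unpooled variance,

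n = (1.960 + 0.842)² × [p1(1 − p1) + p2(1 − p2)] / (p1 − p2)²
= 7.849 × (0.2436 + 0.1716) / 0.20² = 81.5, so 82 per arm.

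Power at 80 per arm is 79.3%. With pooled variance under the null, n is 85 and power at 80 is 77.9%. The stated 80 is therefore reproduced to within a few infants, for any ROP. A minor slip: 22/42 = 0.524, so 42% to 22% is a 47.6% reduction. An exact halving is 42% to 21%, which needs 76 per arm (pooled).

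**Step 2: direction.** Every infant with stage 3 or worse has ROP, so in one population the stage 3 rate cannot exceed the any-ROP rate. For a fixed relative reduction and fixed n, power falls as the control rate falls.

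**Step 3: size, over assumed control rates.** Pooled two-proportion test, two-sided 5%, p2 = p1/2, p̄ = (p1 + p2)/2:

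power = Φ{[(p1 − p2)√n − 1.960·√(2p̄(1 − p̄))] / √(p1(1 − p1) + p2(1 − p2))}

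Example, 20% v 10%, n = 80: (0.894 − 0.990)/0.500 = −0.19, and Φ(−0.19) = 42%.

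The three sample sizes are 80 (the stated evaluable number), 89 (105 × 0.85 = 89.25, deaths removed) and 105 (all enrolled).

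| Assumed control rate | Power, 80/arm | 89/arm | 105/arm | n/arm for 80% |
|---|---|---|---|---|
| 15% | 32% | 35% | 40% | 278 |
| 20% | 42% | 46% | 53% | 199 |
| 25% | 53% | 57% | 64% | 152 |
| 30% | 62% | 67% | 74% | 121 |
| 35% | 72% | 76% | 83% | 99 |
| 40% | 79% | 84% | 89% | 82 |

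**Step 4: control rate needed for 80% power with a halving.** About 40% at 80 per arm, 37.5% at 89 and 33% at 105.

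**Step 5: limit of this check.** These figures are for an unadjusted two-proportion test. The planned primary is a stratum-adjusted Poisson model using follow-up time, and its power can differ. For 42% v 22% with equal follow-up and no covariates, a Wald test on the log rate ratio has about 59% power at 80 per arm and 71% at 105 with model-based Poisson variance, and about 74% and 85% with robust variance. The SAP does not say which variance is used.

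**The case against.** **The protocol already pointed to severe ROP.** Its aims speak of sight-threatening disease and 11.4 refers to stage 3 or more. This stands. A reader might infer that the sponsor moved the primary endpoint without disclosing it, perhaps after the safety committee's review of the first 30 infants. The documents do not support that. The protocol was inconsistent before the SAP was written, the SAP adopted one of its readings, and nothing says that ROP results by arm reached the SAP's authors. What remains is that section 11.1 names any ROP under the primary endpoint heading, and section 6 does not mention the difference.

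**Any ROP is not wholly ignored.** A reader might say that it is never analysed. That goes too far. The SAP covers only the first publication, and all ROP stages are adverse-event categories that will be summarised. The accurate statement is that any ROP has no planned efficacy estimate or test in this SAP.

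**The shortfall may be small.** This stands in part. The 42% is a national figure for 2008–2012. The trial reserves 84 of 210 places for infants up to 24 weeks + 6 days, and the protocol's introduction reports a substantial rise in severe ROP at one hospital. A severe-ROP rate near 35% is not excluded, and with all 105 per arm contributing it would give 83% power. It would be wrong to say flatly that 80% is reached only at about 40%.

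**The pilot.** A reader might set the assumed effect against the sponsor's pilot ("We found no effect of SMOFlipid on ROP outcome"). That does not bear on this point. The pilot tested a different product, under which AA fell further than with Clinoleic, and the protocol gives this as a reason for supplementing AA with DHA.

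**Nothing in the trial changes.** Planned enrolment ended in May 2018 and the SAP is dated November 2019. Restating power cannot alter the sample size, type I error or the estimate, and a 95% confidence interval is already required. That is true, and it is why the remedy is limited to disclosure and one added analysis.

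**Conclusion.** The point holds. The only sample-size and power statement belongs to any ROP, the primary test is of stage 3 or worse, and the documents give nothing from which power for that test can be computed. The direction is certain for the same population, relative reduction and sample size: power is below the any-ROP figure.

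The size is conditional. With a halving and an unadjusted test, power runs from 32–40% at a 15% control rate to 72–83% at 35%, depending on whether 80 or 105 per arm contribute. These control rates are assumptions, and no row of the table is better supported by the documents than another. The slip between 47.6% and 50%, and the 78–79% power at 80 per arm, are minor. The finding is an inconsistency in a figure the trial relies on; it is not evidence of a data-driven change of endpoint.

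**What to change.** 1. **SAP 1.4:** state that the 80% refers to any ROP. Add the power, or the smallest detectable effect, for stage 3 or worse over a stated and justified range of control rates, under the planned stratum-adjusted Poisson analysis and its handling of deaths. Correct the description of 42% to 22% as a 50% reduction.
2. **SAP section 6:** record that the sized endpoint (any ROP) differs from the tested endpoint (stage 3 or worse), and say which protocol sections the SAP followed.
3. **SAP 3.2.2 and 4.6.2:** add any ROP as a named secondary analysis, exploratory and outside the fixed sequence, with the same model as the primary.

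The cost is some SAP text, a short power calculation and one extra model run. No infants are added. The drawback is a less favourable stated power.

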## **5 STUDY SUBJECTS**

### **5.1 Number of Subjects**

For efficacy evaluations, 80 subjects need to be included in each interventional arm for statistical considerations. However, to compensate for protocol violations, mortality and withdrawals up to 105 subjects in each arm will be included (see 11.1 Termination of Sample Size and Statistical Methods on page 26).

After the first 30 subjects have been treated and evaluated there will be a safety check to confirm that the safety profile is acceptable and that the assumption of reduction in ROP incidence is reasonable.

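### The sample-size paragraph labels 42% to 22% a 50% reduction (it is 47.6%), which puts 80 per arm at about 78–79% power, and that power is for any ROP, not for the SAP's primary variable of stage 3 or worse.

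*Combined protocol and SAP*

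**What the plan says.** Protocol 11.1 takes a 42% incidence of any ROP in Swedish infants of matching gestational age (2008–2012), an alpha of 5% and 80% power, and continues: "a 50% reduction in incidence of any ROP, i.e. from 42% to 22%, a sample size of 80 subjects per treatment group is required". It names no test or variance formula and does not say whether alpha is one- or two-sided. Two-sided testing appears in SAP 4.1: "All tests will be two-tailed and confirmed analyses will be conducted at 0.05 level".

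Protocol 5.1 relies on the same size: "80 subjects need to be included in each interventional arm for statistical considerations". Both 5.1 and 11.1 then set enrolment at 105 per arm, to allow for protocol violations and drop-outs. Section 11.1 mentions a death rate of about 15% as an example and gives no figure for violations.

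SAP 1.4 reproduces the protocol paragraph, including "a sample size of 80 subjects per treatment group is required", and identifies it as text from protocol version 7b. SAP 3.2.1 and 4.6.1 define the primary efficacy variable as ROP stage 3 or worse, analysed by Poisson regression adjusted for centre and gestational-age category. SAP section 6 reports no changes from the protocol. Neither document gives an expected rate of stage 3 or worse, or a power for it.

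**The concern.** Two things do not fit together. First, the paragraph equates a 50% reduction with a fall from 42% to 22%. These are different effects and lead to different sample sizes, and 80 lies between them. A reader cannot tell which effect the trial was sized for, or whether 80 evaluable infants per arm carry the stated power.

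Second, the paragraph is the only statement of power in either document, and it concerns any ROP. The SAP tests a more restricted event. Stage 3 or worse is a subset of any ROP, so its rate cannot be higher, and for a fixed relative reduction a lower rate means less power. Someone reading SAP 1.4 alongside SAP 4.6.1 would naturally take 80% as the power of the primary analysis, and nothing in the documents supports that. This matters most if the primary result is not significant, because SAP 4.1 then stops the fixed testing sequence and the result will be read against the stated power.

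**Working it through.** **Inputs.** Control rate 0.42, treated rate 0.22, alpha 5% and power 80% (protocol 11.1); two-sided (SAP 4.1); 1:1 allocation (SAP 1.3). z = 1.960 for alpha and 0.8416 for power; (1.960 + 0.8416)² = 7.849.

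**Effect label.** 1 − 22/42 = 0.476, a 47.6% reduction. Half of 42% is 21%.

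**The plan's own figure, 42% v 22%.** p1(1−p1) + p2(1−p2) = 0.2436 + 0.1716 = 0.4152; mean rate 0.32; difference 0.20.
- Unpooled: n = 7.849 × 0.4152 / 0.20² = 81.5, so 82 per arm.
- Pooled: n = [1.960 √(2 × 0.32 × 0.68) + 0.8416 √0.4152]² / 0.20² = (1.293 + 0.542)² / 0.04 = 84.2, so 85 per arm.
- The arcsine formula gives 84, and the continuity-corrected formula 94.

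**Power at 80 per arm, 42% v 22%.**
- Unpooled: Φ(0.20 / √(0.4152/80) − 1.960) = Φ(0.816) = 79.3%.
- Pooled: Φ((0.20 × √80 − 1.293) / 0.644) = Φ(0.770) = 77.9%.
- Exact enumeration of the uncorrected chi-square test: 78.6%.

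**If a true halving was meant, 42% v 21%.** The variance sum is 0.2436 + 0.1659 = 0.4095.
- Unpooled: 7.849 × 0.4095 / 0.21² = 72.9, so 73 per arm.
- Pooled: 75.6, so 76 per arm.
- Power at 80 per arm: 82.2% (pooled) to 83.5% (unpooled).

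**Planned enrolment.** 105 × 0.85 = 89.25, so about 89 per arm after 15% deaths. Pooled power at 42% v 22% is Φ((0.20 × √89 − 1.293) / 0.644) = 82.2%. The 85 per arm that the pooled formula needs is reached as long as total losses stay at or below 1 − 85/105 = 19%.

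**Primary variable of the SAP.** The documents give no rate of stage 3 or worse, so the control rates below are assumptions. They keep the relative reduction implied by 22/42 and use the pooled two-proportion test with 89 per arm and no covariate adjustment.

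| Assumed control rate, stage 3 or worse | Treated rate (× 22/42) | Power at 89 per arm |
|---|---|---|
| 20% | 10.5% | 42% |
| 30% | 15.7% | 62% |
| 35% | 18.3% | 71% |
| 42% (any ROP, for reference) | 22% | 82% |

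**The case against.** The case for leaving the paragraph alone is reasonable. A reader might infer that the sample size simply fails to reproduce. The documents do not support that: no formula is named, and the standard unpooled formula comes within 2 infants per arm and within 1 percentage point of the stated figures. If the 50% reduction was the intended input, 80 per arm is more than enough. The trial also enrols 105 per arm, not 80, which restores about 82% power for any ROP after 15% deaths. All of this stands, and it makes the arithmetic part minor. It does not make the paragraph consistent: none of the two-sided formulas tried gives exactly 80 for either pair of rates, and all four exceed 80 for the rates named. The reserve must also absorb protocol violations, for which no figure is given.

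A reader might also infer that Poisson regression by itself pulls power well below 80%. That is not established. SAP 4.6.1 names no variance estimator, and the answer depends on it. Taking the any-ROP rates and equal follow-up, exact enumeration at 80, 89 and 105 per arm gives about 63%, 69% and 77% with ordinary model-based variance, but about 77%, 81% and 88% with robust variance. These figures also use any-ROP rates, so neither set is the power of the SAP's primary analysis. They show only that the variance method needs to be stated.

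Finally, SAP 1.4 presents its text as the protocol's, so overwriting it would misreport the source. That is correct, and it shapes the fix.

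**Conclusion.** The point holds at modest size for the arithmetic and more seriously for the endpoint.

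- **Arithmetic.** The stated reduction, rates, power and size do not all hold together. For 42% v 22% the shortfall at 80 per arm is 2 to 5 infants per arm, or about 1 to 2 percentage points of power. Planned enrolment covers it for any ROP if losses stay near 15%. This rests on a two-sided 5% test of two proportions with 1:1 allocation.
- **Endpoint.** The stated 80% does not describe the SAP's primary analysis. How far power falls cannot be fixed from the documents. The range of about 42% to 71% rests on assumed control rates of 20% to 35%, an unchanged relative reduction, 89 evaluable per arm and a simple two-proportion test. A larger effect on severe disease, or a gain from covariate adjustment, would raise it. The introduction to the protocol reports that severe ROP increased at one hospital after the higher saturation target was adopted, but gives no rate.

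**What to change.** **Protocol 11.1:** use one consistent pair of rates, either 42% v 22% described as about a 48% reduction, or 42% v 21% described as a halving. Name the formula and state that alpha is two-sided. Restate the power: for 42% v 22%, 82 to 85 per arm for 80%, about 78–79% at 80 per arm, and about 82% at 89. Align protocol 5.1 with the result.

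**SAP 1.4:** keep the reproduced protocol text and add a note beneath it with the corrected figures. In the same note, give the power for stage 3 or worse under the SAP's Poisson test, with the assumed control rate (or a range) and the variance method stated.

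The cost is wording plus one short calculation. The sponsor has to supply an assumed rate of stage 3 or worse, and the power reported for the primary analysis may look less favourable. Enrolment does not change.
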